### Clinical management

2.6

The patients will be discussed in a multidisciplinary team (MDT) conference based on the results of the scans and staging performed accordingly. If in doubt of metastases, further imaging or biopsy will be performed if possible and relevant. The MDT will suggest a treatment strategy that follows the contemporary national guidelines.^15^ In a shared decision process with the patient, the final choice of treatment will be decided upon, and the patients may be treated by prostatectomy, radiotherapy, androgen deprivation therapy (ADT), chemotherapy or antiandrogens and, eventually, in combinations.

### 
QoL

2.7

QoL will be assessed using the following widely used questionnaires—all of them were translated and cross‐culturally validated in Danish:
Functional Assessment of Cancer Therapy‐Prostate (FACT‐P)—39 items^16^;European Quality of Life‐Five Dimensions (EQ‐5D‐5L) covering five dimensions: mobility, self‐care, usual activities, pain/discomfort and anxiety/depression—25 items and a VAS scale^17^, ^18^, ^19^; andThe Expanded Prostate Cancer Index Composite (EPIC‐26)—26 items.^20^
The patients will be asked to fill in the questionnaires electronically or on paper at fixed time points in their pathway (at diagnosis and after 3, 6, 12, 24, 60, 120 and 234 months after enrolling—enabling data collection for approximately 20 years after inclusion of the last patient). Time points of evaluation are chosen to be able to evaluate QoL over time after diagnosis and treatment.

## PRIMARY AND SECONDARY ENDPOINTS

3

The primary endpoint, PFS, will be compared between Groups A and B and defined as the time from inclusion to progression (Appendix C) or death for any reason. Progression is defined as clinical or biochemical recurrence/progression. Progression can be considered with or without progression on imaging or change in treatment. After prostatectomy, a confirmed rise of PSA (two following rising PSA values according to Prostate Cancer Working Group 3 [PCWG3]^21^, ^22^) above 0.2 ng/mL for patients with unmeasurable PSA value after prostatectomy will deem progression. For patients after radiotherapy, a confirmed rise in PSA value above 2 ng/mL from nadir defines recurrence. Patients with measurable PSA after prostatectomy and subsequent referral to salvage radiotherapy for completion of treatment will not be categorised as having progression but as having residual disease (Appendix D). Residual disease will be a secondary endpoint compared between the two groups too.

Progression is determined for patients undergoing palliative treatment with a subsequent confirmed rising PSA and/or progression on imaging, leading to initiation or change of treatment.^23^

The distribution of disease stage and treatment strategy will be evaluated between the two groups as secondary endpoints. Overall survival is a secondary endpoint too and will be evaluated between Groups A and B after suitable time spans, expected after 5, 10, 15 and 20 years. Regarding QoL, changes from baseline to 12 months are of primary interest, and an 8‐point decline in the global FACT‐P score will be considered clinically relevant. We suggest that more sensitive and suggestively correct staging will lead to improved QoL, because the treatment initiated is expected to better fit each patient. For example, small metastases that might not be identified with Na[^18^F]F‐PET/CT can be taken into account and leave the patients with less unattended small metastatic lesions and hence avoiding initial curative intended treatment with possible side effects for patients with primary disseminated disease.

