## Appendix D DEFINITIONS OF RECURRENCE AND PROGRESSION^15^

**Table jats-table-wrap-3:**

**Recurrence after prostatectomy**	PSA rising from unmeasurable to above 0.2 ng/mL in two following measurements.
**Recurrence after radiotherapy**	PSA rising with 2 ng/mL above nadir in two following measurements.
**Progression**	PSA rising in two following measurements AND/OR progression on imaging AND/OR clinical progression.
**Castration resistance**	Progression despite of castration.

Abbreviation: PSA, prostate‐specific antigen.

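### Clinical progression alone, with no criterion, counts as a primary PFS event under one rule in the protocol and not under another, and the treating teams know the staging scan

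*Protocol article*

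**What the plan says.** Section 3 (Primary and secondary endpoints) defines PFS as time from inclusion to progression or death from any cause. Its general rule is: "Progression is defined as clinical or biochemical recurrence/progression. Progression can be considered with or without progression on imaging or change in treatment".

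The same section gives PSA thresholds after prostatectomy (0.2 ng/mL) and after radiotherapy (2 ng/mL above nadir). For patients on palliative treatment it sets a different rule: "subsequent confirmed rising PSA and/or progression on imaging, leading to initiation or change of treatment".

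Appendix D defines progression as: "PSA rising in two following measurements AND/OR progression on imaging AND/OR clinical progression".

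Section 2.6 (Clinical management) says that patients are discussed at a multidisciplinary conference "based on the results of the scans and staging performed accordingly". The Discussion states that treatment proportions are not expected to balance between the arms. It lists the differing definitions of progression as a limitation, but does not mention assessors' knowledge of the scan.

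**The concern.** PSA-defined events and deaths follow a rule that anyone can apply to the record. Clinical progression does not: the article gives no criterion for it and expressly waives two possible anchors, imaging and treatment change. The teams who see the patients know which scan was used. The article also records an expectation about the arms: that NaF staging may miss small metastases (section 3), and that some NaF-staged patients relapse soon after curative treatment (Discussion). An ambiguous symptom could be labelled differently in the two arms on that basis.

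The conflict between the general and the palliative rule adds to this. If palliative treatment is more common in one arm, the clinical-only route is open to a different share of patients in each arm, depending on which sentence is followed. At stake is whether a PFS difference can be attributed to staging and its consequences, or partly to how progression was declared.

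**Working it through.** **1. The passages side by side**

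| Place | Clinical progression alone counts? | Treatment change needed? |
|---|---|---|
| Section 3, general rule | Yes | No |
| Section 3, palliative treatment | No: PSA rise and/or imaging | Yes |
| Appendix D, progression | Yes | Not mentioned |

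The first and third rows cannot hold together with the second for a palliative patient. The cross-references do not settle it: section 3 points to Appendix C for progression, but Appendix C lists the endpoints, and the definitions are in Appendix D.

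**2. The plan's own figure**

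Inputs from section 3.2: hazards 0.5 and 0.35 (taken as per year), 3 years of accrual, 1 year minimum follow-up, two-sided 5%, power 80%.

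Event probability under uniform accrual: p = 1 − [exp(−h) − exp(−4h)]/(3h). This gives 0.686 at h = 0.5 and 0.564 at h = 0.35.

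An exponential test on the hazard difference with pooled null variance gives N = 401.6, so the stated 402 is reproduced. Then 201/0.9 = 223.3, rounded up to 224 per arm, or 448. The sample size is not in dispute.

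Expected events in 402 patients: 201 × (0.686 + 0.564) ≈ 251.

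**3. How much differential labelling could matter**

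The document gives neither the share of clinical-only events nor any shift in labelling. Both are assumptions here. Let s be the clinical-only share and d the relative shift, up in Group A and down in Group B, with no true difference between arms:

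- apparent HR = (1 − sd)/(1 + sd)
- z = ln(HR) × √251/2
- chance of a false PSMA win = Φ(−1.96 − z); chance of a false control win = Φ(−1.96 + z)

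| s | d | HR | z | False PSMA win | False control win | Two-sided total |
|---|---|---|---|---|---|---|
| 0 | 0 | 1.00 | 0 | 2.5% | 2.5% | 5.0% |
| 5% | 10% | 0.99 | −0.08 | 3.0% | 2.1% | 5.1% |
| 10% | 20% | 0.96 | −0.32 | 5.0% | 1.1% | 6.2% |
| 20% | 20% | 0.92 | −0.63 | 9.2% | 0.5% | 9.7% |

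Totals are taken before rounding. With hazard 0.5 in both arms the event count is 402 × 0.686 ≈ 276, and the false PSMA win becomes 3.0%, 5.2% and 9.8%, so the choice of event count matters little. If the shift ran the other way, the two tails would swap.

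**4. Events left in an analysis without clinical-only progressions**

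Removing 5%, 10% or 20% of 251 removes about 13, 25 or 50 events and leaves about 238, 226 or 201. With power = Φ(√D/2 × |ln 0.7| − 1.96), power at HR 0.7 goes from 81% at 251 events to about 79%, 76% and 71%. This overstates the loss, because some of these patients would later have a PSA or imaging event or die.

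**The case against.** The strongest reply is that every pathway already has a rule-based trigger: PSA thresholds after prostatectomy and radiotherapy, and PSA and/or imaging with a treatment change under palliation. On that reading, clinical-only events would be few. This stands in part. It rules out saying that the clinical-only route plainly covers all patients. But the PSA thresholds sit beside the clinical route and do not replace it, and the palliative sentence contradicts the general rule without overriding it.

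A reader might infer more than the document supports:

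- **That PFS events are judged by unmasked staff.** The article does not say who classifies progression. Knowledge of the scan follows from section 2.6 for the treating teams only, and the full protocol may describe masked review.
- **That no sensitivity analysis is planned.** A condensed article would commonly leave this to the analysis plan, so its absence is no finding.
- **That no definition of clinical progression exists anywhere.** Appendix D cites the national guideline and section 3 cites working-group criteria. These cannot be checked here.
- **That PFS is biased towards PSMA, or that a small advantage would be falsely declared.** The direction is not derivable from the document. With 251 events, significance needs an observed HR of about exp(−1.96 × 2/√251) = 0.78, so an apparent HR of 0.92 to 0.96 would not by itself be significant.

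The model in the working is also crude. A patient labelled early who later meets the PSA rule changes only the event time, so the bias could be smaller than shown. Even as shown, the low case is trivial and the middle case adds about one percentage point to two-sided error.

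**Conclusion.** The point holds as a badly fixed event definition. Two places allow clinical progression alone, without a criterion, as a primary event, and a third excludes it for palliative patients. Because treatment is expected to differ by arm, the inconsistency is not neutral between arms.

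How far this would move the PFS comparison is unknown. Over the assumed range (5% to 20% clinical-only events, 10% to 20% shift), the false PSMA-win tail is about 3% to 9% against 2.5%, and total two-sided error about 5.1% to 9.7% against 5%. Those figures rest on the assumed shares and shifts, on opposite shifts in the two arms, and on shifted events being gained or lost for good. They illustrate sensitivity and do not estimate the bias in this trial.

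**What to change.** 1. Reconcile the general sentence in section 3, its palliative sentence and Appendix D into one PFS event definition, applied identically in both arms, and correct the appendix references. Which clinical rule to adopt is for the investigators.
2. Record the basis of each PFS event: PSA, imaging, clinical only, or death.
3. Pre-specify one Cox PFS analysis, with the same adjustment as the primary model, in which clinical-only progressions are not counted as events and the patient stays at risk. Report it beside the primary analysis, and qualify the PFS claim if its conclusion differs.

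The cost is one field on the event form, one further model and somewhat fewer events in that sensitivity analysis (about 13 to 50 of 251 under the assumed shares). Sample size, treatment and follow-up do not change. A masked review of reported clinical-only events is not asked for: it adds a procedure and could not recover events that were never reported.

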## DISCUSSION

4

Several studies have shown that PSMA‐PET/CT is superior to BS and CECT for detecting relapse of PCa, and PSMA‐PET/CT is introduced in the guidelines for this indication.^24^, ^25^ The first studies on PSMA‐PET/CT for primary staging of PCa have been published, showing higher sensitivity to detecting metastases than BS and CECT.^26^, ^27^ PSMA‐PET/CT is only cautiously introduced in the international guidelines for primary staging of intermediate‐ and high‐risk PCa patients because of lack of evidence of whether the increased sensitivity will translate into patient benefit of being staged with this more sensitive modality.^11^

Hofman et al. have performed a large randomised controlled study in a cross‐over design.^9^ They randomised the patients in two groups: One group was initially staged with conventional imaging (BS and CECT) and another group with [^68^Ga]Ga‐PSMA‐11 PET/CT. If less than three metastases were found in either group at initial staging, the patients crossed over to the other group and a new staging was performed. Follow‐up was performed clinically and with imaging in up to 2 years after the recruitment of the last patient. They found that [^68^Ga]Ga‐PSMA‐11 PET/CT had higher accuracy than conventional imaging, and a change of treatment strategy was seen in 27% of patients initiating with conventional imaging, whereas 5% changed treatment strategy after crossing over to conventional imaging. However, the study was not designed to provide information on patient benefit of using PSMA‐PET/CT as frequently requested, for example, in the international guidelines.^11^ Information such as the gain in PFS, residual disease after treatment with curative intent and QoL is still lacking.

In this study, we hypothesise that staging patients with PSMA‐PET/CT will lead to a longer PFS. Today, a significant group of PCa patients are diagnosed with residual disease after prostatectomy.^28^, ^29^ We believe that more sensitive imaging for primary staging will reduce this rate because of more correct initial staging and improved treatment for the individual patient, and ultimately a longer PFS, a longer overall survival, and improved QoL.

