We expect stage migration in a group of patients staged with [^18^F]PSMA‐1007‐PET/CT, where small lymph node metastases may be found in the pelvis or along the abdominal aorta—metastases that would not have been detected with CECT because of their small size. These patients will be presented at MDT conferences and, here, the conclusion may end up with a change from the standard treatment (with curative intent) to an individualised treatment towards both the prostate gland and the lymph node metastases locally or distant; hence, the treatment may include surgery as well as radiation and ADT. Because of possible stage migration in the PSMA group, we do not expect that the treatment proportions will balance between the two arms. Our observation from current clinical practice is that some patients staged with Na[^18^F]F‐PET/CT experience residual disease or recurrence short time after initial treatment with curative intent. These patients are currently being referred to a [^18^F]PSMA‐1007‐PET/CT to detect residual disease or metastases.

The recommendations for treatment have changed over the last decade^11^ and with current opportunities, even localised treatment of a solitary metastasis may be considered relevant.^30^ This means that using sensitive procedures for primary staging should be considered even more important than ever before.

The strengths of this study are the prospective design in a multicentre setting and with clinically and patient‐relevant outcomes. We have replaced conventional BS with Na[^18^F]F‐PET/CT clinically in the participating centres in this project, which may be considered a limitation because the majority of clinical trials have used BS for treatment planning. However, as Na[^18^F]F‐PET/CT is not proven more sensitive than BS and CECT, we believe that the results will still be relevant for centres using BS and CECT for staging.

The fact that we expect some patients in the PSMA arm to be up‐staged, a higher selection of patients in the PSMA group will be offered treatment with curative intent. This will affect the comparability of the groups with respect to defining PFS, which is a limitation to the study. The different treatment options offered to the patients over a long period of time after the diagnosis could be considered a limitation too, as well as the different definitions of progression according to the different treatments.

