**Secondary endpoints**	
Group A versus Group B	Stage distribution; Treatment distribution; Frequency of residual disease; QoL; Overall survival

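### Residual disease can arise only after prostatectomy, yet its frequency is compared between the randomised arms while the scan influences who is operated on, so a difference would not by itself show better treatment

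*Protocol article*

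**What the plan says.** Section 3 (Primary and secondary endpoints) places residual disease within surgery: "Patients with measurable PSA after prostatectomy and subsequent referral to salvage radiotherapy for completion of treatment will not be categorised as having progression"; such men are classed as having residual disease instead. It cites Appendix D for this, but Appendix D has no entry for residual disease. The section then adds: "Residual disease will be a secondary endpoint compared between the two groups too". Appendix C lists "Frequency of residual disease" among the Group A versus Group B secondary endpoints. Section 3.2 assigns categorical variables a chi-squared test and sets the level at two-sided 5%.

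Section 2.6 (Clinical management) has the conference discuss each man on the basis of his scan and suggest a strategy. After a shared decision, "the patients may be treated by prostatectomy, radiotherapy, androgen deprivation therapy (ADT), chemotherapy or antiandrogens and, eventually, in combinations".

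The Discussion expects this to differ by arm: "we do not expect that the treatment proportions will balance between the two arms". It names loss of comparability as a limitation for PFS only. It also states the belief that more sensitive staging will lower the rate of residual disease through more correct staging and improved treatment.

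**The concern.** A man who is never operated on cannot meet the definition. Whether he is operated on is partly a consequence of the scan to which he was randomised. The endpoint is therefore defined only within a group formed after randomisation, and its frequency can move for two separate reasons: a different number or type of men reach surgery, or surgery leaves less disease behind.

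Only the second reason, or evidence that men moved to other treatment fared better, would bear out the improved treatment that the Discussion hypothesises. A single frequency per arm with a chi-squared test cannot separate the two. The wording also varies: the Discussion speaks of "residual disease after treatment with curative intent and QoL is still lacking", which would take in radiotherapy, whereas Section 3 confines the endpoint to prostatectomy.

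**Working it through.** **The plan's own figures.** The article gives no expected rate or sample size for residual disease. The only trial size borrowed here is 224 per arm (Section 3.2), which reproduces: 201/0.9 = 223.3, rounded up to 224. The PFS calculation is not affected by this point.

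**Inputs from the article.** Appendix E, labelled a mock, gives N0M0 shares of 55% (NaF) and 45% (PSMA).

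**Assumptions, none of them from the article.**
- Only men staged N0M0 are operated on, and a fraction q of them, with q = 0.5 or 1.
- Residual risk if operated on is 15% for the 45% of men who would be N0M0 on either scan.
- Residual risk is r = 40%, 60% or 80% for the 10% of men whom only PSMA would upstage.
- Each man has the same surgical result in whichever arm he is operated on.

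**Operated men only.**
- Rate in A = (0.10r + 0.45 × 0.15)/0.55. For r = 0.4 this is 0.1075/0.55 = 19.5%; for r = 0.6, 0.1275/0.55 = 23.2%; for r = 0.8, 0.1475/0.55 = 26.8%.
- Rate in B = 15%, because the upstaged men are no longer in the operated group.
- Men operated on at q = 1: 224 × 0.55 = 123.2 and 224 × 0.45 = 100.8. At q = 0.5: 61.6 and 50.4.

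The chance of p<0.05 is approximately Φ((d − 1.96·s0)/s1), where d is the difference, s0 its pooled standard error and s1 its unpooled standard error. For r = 0.8 and q = 1: d = 0.1182, s0 = 0.0552, s1 = 0.0535, giving Φ(0.19) = 57%.

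| r | A vs B, operated only | Chance of p<0.05, q = 0.5 | Chance of p<0.05, q = 1 |
|---|---|---|---|
| 40% | 19.5% vs 15% | 9% | 14% |
| 60% | 23.2% vs 15% | 19% | 33% |
| 80% | 26.8% vs 15% | 32% | 57% |

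If the residual risk were the same for every man, the operated-only rates would be equal. The gap in the table is entirely selection.

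**All randomised men.** Frequency = share operated on × residual risk per operated man. With a flat 20% risk and q = 0.5, A is 0.55 × 0.5 × 0.20 = 5.5% and B is 0.45 × 0.5 × 0.20 = 4.5%. The arms differ although the outcome per operation is identical. This is a true effect of the staging strategy, but it comes wholly from the number of operations.

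**Direction.** Section 3 foresees PSMA finding small metastases and "hence avoiding initial curative intended treatment with possible side effects for patients with primary disseminated disease", which means fewer such treatments. The Discussion says that "a higher selection of patients in the PSMA group will be offered treatment with curative intent", which means more. If the second meant more operations, for example 60% rather than 50% of men N0M0 in the PSMA arm with q = 0.5 and a 20% risk, the all-randomised frequency would be 0.50 × 0.5 × 0.20 = 5.0% in A and 0.60 × 0.5 × 0.20 = 6.0% in B, against PSMA.

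**The case against.** The strongest reply is that the trial compares staging strategies, so treatment choice is part of what is being tested. Fewer randomised men left with residual disease after surgery is then a legitimate randomised effect, and sparing men with disseminated disease an operation is an intended mechanism. This stands. A reader might infer that the all-randomised comparison is biased too, or that its chance of significance is a false-positive rate. The documents do not support that: it is valid, but hard to interpret alone.

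Other replies also hold in part.
- The choice of denominator could sit in a full protocol or analysis plan that is not shown, so its absence from the article is not the point. Naming a denominator would not resolve the difficulty, because the definition and the between-arm comparison are fixed here.
- The Discussion states a hypothesis about mechanism, not a rule that a lower rate proves benefit. PFS, overall survival and quality of life are compared separately.
- Nothing gives an operated-only comparison confirmatory status, or says that it is the planned analysis.
- Treatment distribution is already a between-arm secondary endpoint and would expose much of the imbalance if read beside residual disease. It would not show the two jointly.
- The mention of curative intent in the Discussion describes what earlier research left unknown, and the trial's own hypothesis nearby refers to prostatectomy. The mismatch in wording is minor.
- Surgery may be given in combinations, and the Discussion allows it for men with PSMA-detected nodes, so the N0M0-only premise of the illustration is a simplification.

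**Conclusion.** The concern holds in a limited form. Residual disease is defined only after prostatectomy, is compared between the randomised arms, and depends on a treatment choice that the scan influences. An operated-only comparison can differ by selection alone. An all-randomised comparison is valid for the strategy but does not by itself show improved treatment.

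The illustrated size is 19.5% to 26.8% versus 15% among operated men, with about a 9% to 57% chance of p<0.05 and no change in any operated man's outcome. These figures rest on a mock table, unsourced risks, and half to all N0M0 men being operated on. They show that the effect is possible; they are not a forecast.

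A reader might infer that the endpoint is set to favour PSMA. The documents do not support that, because Section 3 and the Discussion expect opposite shifts in curative-intent treatment. Those two statements need to be reconciled. This is a secondary endpoint and the primary analysis is untouched, but the change is worth making because the Discussion ties a lower rate to improved treatment.

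**What to change.** 1. Analyse the endpoint in all randomised men as three levels: prostatectomy with residual disease, prostatectomy without residual disease, and no prostatectomy. Report the three proportions by arm with confidence intervals.
2. Report the rate among operated men as descriptive. Label it as conditional on treatment chosen after randomisation and not as evidence of benefit.
3. Extend the comparability limitation in the Discussion from PFS to residual disease, and reconcile the Discussion with Section 3 on the expected direction of curative-intent treatment.
4. Use one definition of residual disease in Section 3, the Discussion and Appendix C, and correct the reference to Appendix D or add the entry there.

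The data are those already needed for the treatment-distribution and residual-disease endpoints, and no treatment rule changes. The cost is wording, slightly more analysis, and giving up a between-arm test of the operated-only rate.
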